# Feasibility of an Intervention Targeting Health through Exergaming as an Alternative to Routine Treatment (FIT HEART): protocol for a non-randomised two-armed pilot study

**DOI:** 10.1186/s40814-022-01068-2

**Published:** 2022-06-11

**Keywords:** Exergaming, Active videogaming, Physical activity intervention, Mental health, Inpatient, Cardiovascular, Cardiometabolic risk

## Abstract

**Background:**

Despite elevated risk of cardiometabolic disease among those with serious mental illness, and widespread recognition that physical activity interventions are required, there are multiple barriers to implementing typically recommended physical activity programmes in secure inpatient settings. Due to low mood, negative symptoms and poor socio-occupational functioning, psychiatric inpatients often lack motivation to engage in physical activity programmes. Moreover, regular access to outdoor spaces and exercise equipment is limited. As such, there is a need for novel physical activity interventions that are suitable for secure settings. This study aims to investigate the feasibility, acceptability and potential effectiveness of an intervention (exergaming) to promote physical activity among patients in a secure mental health setting.

**Methods:**

This non-randomised, two-arm pilot study will employ a pre-test/post-test parallel group design, comparing the exergaming intervention with a “routine treatment” control. Two high-secure, sub-acute wards in the Long Bay Hospital Mental Health Unit will be non-randomly allocated to either the exergaming intervention or the “routine treatment” control group.

The intervention group will receive a 12-week programme comprising three 30-min exergaming sessions per week using various Xbox Kinect^TM^ activity-based games designed to simulate moderate intensity exercise. The “routine treatment” group will continue to receive the standard model of care delivered by the Justice Health and Forensic Mental Health Network. Accelerometers will be distributed to all participants to collect daily energy expenditure, number of steps taken, intensity of physical activity and heart rate data throughout the study.

The primary outcomes are (1) intervention feasibility and acceptability, and (2) baseline to post-intervention changes in physical health outcomes (levels of physical activity; cardiovascular fitness; clinical measures of cardiometabolic risk). Secondary outcomes are baseline to post-intervention changes in mental health outcomes (depression, anxiety, stress, positive psychiatric symptoms). Outcomes will be assessed at baseline, mid-intervention, and post-intervention.

**Discussion:**

This research will contribute to evidence-based practice in the care of patients with serious mental illness: a vulnerable population with complex physical and mental health needs and a markedly elevated risk of cardiovascular disease. The findings will inform cardiovascular health promotion strategies and the implementation of physical activity interventions in secure inpatient settings.

**Trial registration:**

ANZCTR, ACTRN12619000202167. Registered on 12 February 2019, https://www.anzctr.org.au. ANZCTR mandatory data items comply with the minimum dataset requirements of the World Health Organisation (WHO). The ANZCTR contributes trial registration data to the WHO International Clinical Trials Registry Platform (WHO ICTRP).

**Supplementary Information:**

The online version contains supplementary material available at 10.1186/s40814-022-01068-2.

## Background

The adverse metabolic effects associated with psychotropic medications used to treat mental illness are well-documented. Clinically significant weight gain is commonly observed following the commencement of pharmacotherapy for mood and psychotic disorders—particularly treatment with antipsychotics. Disturbances in glucose and lipid metabolism, either secondary to weight gain or via direct mechanisms, are also associated with such medications [1, 2]. In addition to lifestyle factors (e.g. smoking, poor diet, lack of physical activity), these medication side effects increase the risk of metabolic syndrome (MetS) and, in turn, type 2 diabetes and cardiovascular disease. Accordingly, the prevalence of MetS is elevated among those treated with psychotropic medication compared to the general population [3].

There is a growing evidence base for the role of physical activity in improving health outcomes in psychiatric populations, with systematic reviews and meta-analyses of the literature suggesting that exercise interventions can effectively improve cardiorespiratory fitness and reduce cardiometabolic risk [4–6]. Implementing lifestyle interventions in a psychiatric inpatient setting, however, particularly that of a secure mental health unit, presents many challenges. Environmental barriers to physical activity include restricted time in outdoor and communal spaces and limited access to exercise equipment. Moreover, psychiatric inpatients often lack the motivation to engage in physical activity secondary to low mood, negative symptoms and poor socio-occupational functioning. As such, there is a need for novel physical activity interventions suitable for patients in secure settings that will overcome such barriers.

Research into the utility of “exergaming” as a form of physical activity has shown promising results. Exergaming refers to active video games that use the player’s movement to control the game. Laboratory-based experimental studies of the acute effects of exergaming have demonstrated increased energy expenditure, heart rate and oxygen consumption at an exertion level equivalent to “moderate intensity” exercise [7, 8], depending on the nature of the game and extent of lower body involvement [9]. Intervention studies indicate that exergaming results in increased energy expenditure, improved cardiovascular fitness and increased muscle strength, in addition to a decrease in body weight, waist circumference, and body fat percentage [10–12]. Positive effects on mood, motivation to exercise and cognitive functioning have also been demonstrated [2, 13]. While research among psychiatric populations is limited, pilot data on feasibility, acceptability, adherence and safety validate the integration of exergaming into physical activity programmes for people with serious mental illness. Specifically, intervention trials among people with schizophrenia have demonstrated active videogaming to be an acceptable and enjoyable alternative to other forms of physical activity, with high adherence and retention rates observed among participants [13–18].

Whilst previous research suggests that exergaming-based interventions are feasible and acceptable among psychiatric patients in an outpatient setting [14, 18, 19], there has been no research investigating the feasibility and acceptability of exergaming in an inpatient setting. Moreover, the clinical effectiveness of such interventions in promoting the cardiovascular health of this particular patient population has not yet been investigated. The few studies investigating the health benefits of such interventions for psychiatric populations have typically used a predominantly outpatient sample and have only focused on the amount and frequency of physical activity and functional fitness (e.g. balance, strength, flexibility, mobility) as study outcomes, rather than cardiorespiratory fitness measures and cardiometabolic parameters [14, 18, 19].

### Study aims and objectives

This pilot study aims to investigate the feasibility, acceptability and potential effectiveness of a novel intervention (exergaming) to promote physical activity among patients of a secure mental health unit. The results will inform the design and methodology of a subsequent randomised controlled effectiveness trial.

The specific objectives of the study are to:Determine whether the pilot exergaming programme (FIT HEART) is a feasible intervention for improving physical activity levels among patients in a secure mental health unit, as measured by recruitment rates, retention in the programme, protocol adherence, and patient and staff acceptability ratings.Assess whether participants who receive the FIT HEART programme demonstrate greater improvements in physical activity levels and clinical physical health measures (anthropometry; blood parameters; blood pressure), compared to those who receive routine treatment only.

Based on the emerging evidence, it is hypothesised that the FIT HEART programme exergaming will be a feasible and acceptable form of physical activity intervention among this patient group. Findings on the potential effectiveness of the intervention as an adjunct to routine care in providing physical and mental health benefits to patients will inform hypotheses for a future randomised trial.

## Methods

### Study design

The proposed research will be conducted as a non-randomised, two-arm pilot study comparing an exergaming intervention with a “routine treatment” control. The study will employ a pre-test/post-test parallel group design. Two sub-acute wards from the Long Bay Hospital Mental Health Unit will be non-randomly allocated to either the intervention or control group. Allocation will be based on available facilities (i.e. space, audiovisual equipment) to implement the intervention.

The study duration will be 24 months and will be reported in accordance with guidelines for reporting the protocols of pilot and feasibility studies [20], adapted for a non-randomised design [21], using relevant items from the Standard Protocol Items: Recommendations for Interventional Trials (SPIRIT) checklist [22] (see Additional file 1).

### Setting

The study will be conducted in two sub-acute units of the Long Bay Hospital Mental Health Unit, located at the Long Bay Correctional Complex in New South Wales (NSW), Australia. The Long Bay Hospital Mental Health Unit is a 40-bed inpatient facility that provides specialty mental health services for correctional and/or forensic patients within the Justice Health and Forensic Mental Health Network (JHFMHN). The two sub-acute units house 15 male patients each.

### Participants

The sample will comprise 60 adult patients admitted to the Long Bay Hospital Mental Health Unit (intervention group: 30 patients; control group: 30 patients). All patients aged 18 years and over that are currently admitted to the Long Bay Hospital Mental Health Unit will be given the opportunity to participate in the study, subject to meeting eligibility criteria.

#### Eligibility criteria

Potential participants will be screened for eligibility by members of the FIT HEART project team. The team is based at the JHFMHN Research Unit and comprises experienced researchers with qualifications in nursing, psychology, forensic mental health, and exercise physiology. Screening will entail the following: (i) assessment by the FIT HEART project team of capacity to provide informed consent; (ii) assessment by the treating team of security risk and risk factors that could prevent participants being issued an accelerometer; (iii) screening by the FIT HEART project team and clinical assessment by a medical officer of physical contraindications to exercise.

Patients will be excluded from the study if they meet the any of the following exclusion criteria:Risk factors that could prevent patients being issued an accelerometer (e.g. at risk of self-harm; acute paranoid delusions).Inability to provide informed consent due to acute mental illness, severe cognitive impairment or severe intellectual disability.Insufficient English fluency to provide informed consent and/or complete the pre- and post-test interviews.Unable to participate due to high security risk, as determined by the treating team.Physical contraindications to exercise.

### Eligibility screening and consent procedures

The study will be introduced to patients and staff from the selected units via an oral presentation delivered by the FIT HEART project staff and posters containing information on the nature and purpose of the study which will be displayed in the units.

A pre-screening risk assessment for patients in both the intervention and control units will be conducted by a member of the treating team to ascertain whether the patient is a high security risk (exclusion criterion 4) or has any risk factors that could prevent them being issued an accelerometer to wear during the study period (exclusion criterion 1). Any patients deemed to have risk factors that preclude them from wearing an accelerometer or that are identified as a high security risk will not undergo further screening and will be excluded from the study.

All potential participants eligible for further screening will be provided with a participant information sheet (PIS) detailing the nature and aims of the study at an appropriate level of readability, determined by the Flesch Reading Ease formula [23]. Those who are interested in being screened for study eligibility will be assessed for their capacity to consent (exclusion criterion 2) to the screening process, using the University of California, San Diego Brief Assessment of Capacity to Consent (UBACC) [24] tool. If deemed capable, participants will be asked to provide written consent for all screening procedures.

The screening procedure will comprise the following steps (Fig. 1):An assessment of medical conditions that may increase the risk of an adverse event. This will involve completion of a modified version of the Adult Pre-Exercise Screening System (APSS) Tool, a three-stage screening instrument developed by Exercise and Sport Science Australia, Fitness Australia and Sports Medicine Australia [25]. This questionnaire identifies symptoms and/or diagnoses of cardiovascular, metabolic, respiratory and other diseases, as well as musculoskeletal conditions that may be exacerbated by physical activity (stage 1). The tool also considers risk factors (e.g. age, family history of cardiovascular disease, current activity levels and smoking) before categorising the participant as either low or moderate risk (stage 2). The APSS Tool will be administered by one of the research team.A clinically trained member of the research team will conduct a review of the patient’s medical file identifying current medical and psychiatric conditions, current and past medications and electrocardiogram results.A medical officer will conduct an assessment of medical fitness to participate in an exercise programme (exclusion criterion 5), based on risk factors identified during administration of the APSS Tool, contraindications to exercise arising from prescribed medications, and known medical/psychiatric history. If the medical officer deems the participant inappropriate, they will be excluded from the study.

**Fig. 1 Fig1:**
[figure not shown]
Flowchart of participant eligibility screening and consent

Patients who screen eligible for participation will be asked to provide further written consent for all study procedures, with their capacity to consent assessed a second time with the UBACC tool. One of the research team will witness the signing of all consent forms. Reasons for participant ineligibility and refusal to participate for eligible patients will be documented in a screening log.

### Interventions

#### Exergaming

Participants enrolled in the intervention group will receive a 12-week exergaming programme, delivered by members of the FIT HEART research team who will undergo project-specific training and will be provided with a manual detailing all study procedures. The programme comprises three 30-min exergaming sessions per week for 12 weeks using activity-based games designed to simulate moderate intensity exercise. The exergaming programme will be delivered via Xbox Kinect^TM^ video gaming consoles, with face-to-face supervision of all sessions provided by the FIT HEART research team, nursing staff and unit-based Corrective Services NSW officers. The Xbox Kinect^TM^ system has a large variety of games available, all of which can be played without any equipment (e.g. hand-held controllers). The absence of controllers will minimise the risk of harm to the participants and others. All games to be used in the sessions have been tested by the research team to ensure that a moderate intensity heart rate can be achieved. Selected games include those based on sports, fitness and adventure games (e.g. Kinect Sports, Kinect Adventures, MotionSports Adrenaline, Your Shape: Fitness Evolved, Kinect Rush), dance/rhythm simulation (e.g. Black Eyed Peas Experience, Dance Central) and “party” games (e.g. Raving Rabbids: Alive and Kicking). Each 30-min session will be preceded by a 10-min warm-up utilising one of the lower intensity exergames (e.g. ten-pin bowling, Kinect Joy Ride) and will be followed by a 5-min cool-down, with a choice of stretches designed by an Exercise Physiologist. At 10-min intervals during each exergaming session, participants will be asked to rate their perceived intensity of physical activity using the OMNI-Walk/Run Scale of Perceived Exertion [26] and report the current heart rate displayed on their accelerometer. These measurements will be recorded by the supervising member of the research team. If a participant’s heart rate is not in the moderate intensity range, or if they are seen to be not participating in the game, they will be encouraged to try and increase their intensity or swap to another game.

The intervention protocol is based on current Australian guidelines for physical and sedentary activity. The Australian Government Department of Health recommend that adults (18–64 years) accumulate 150–300 min of moderate intensity or 75–150 min of vigorous intensity physical activity (or an equivalent combination of moderate and vigorous activity) per week. For those who are not currently engaged in regular physical activity, however, a gradual increase in frequency and intensity is recommended [27]. The proposed protocol is also supported by international clinical guidelines for the treatment of mental illness which recommend physical activity programmes consisting of thrice-weekly exercise sessions for a duration of 12 weeks as a low-intensity psychosocial intervention for subthreshold or mild-moderate depression [28].

#### Routine treatment

Enrolled participants on the control unit will receive “routine treatment”, defined as the standard model of care provided by JHFMHN (i.e. usual care). Structured physical activity (e.g. organised walking, gym sessions) over the 14 weeks of monitoring that occurs outside of the assessment periods will be recorded.

### Outcomes

#### Primary outcomes

Intervention feasibility and acceptabilityBaseline to post-intervention changes in physical health outcomes:Levels of physical activityCardiovascular fitnessAnthropometric measures of cardiometabolic risk: weight, body mass index (BMI), waist and hip circumferenceBiomarkers of cardiometabolic risk: blood pressure, blood glucose levels, lipid profiles

#### Secondary outcomes

Baseline to post-intervention changes in mental health outcomes:Symptoms of depression, anxiety and stressPositive psychiatric symptoms

### Participant timeline

The study will be conducted over 14 weeks, including a 12-week intervention period. Participants will be assessed on three occasions: baseline, mid-intervention (week 6) and post-intervention (weeks 13–14). In cases where a participant is discharged from the control or intervention unit, or discontinues their participation, prior to completion of the intervention period (i.e. before week 12), post-intervention assessments will be administered, where feasible. Full details of the timeline and schedule of assessments are presented in Table 1.

**Table 1 Tab1:** Schedule of enrolment, intervention and assessments

	Study period	***Pre-screening***	***Screening***	***Baseline***	***Intervention*** (exergaming or usual care)	***Intervention mid-point***	***Early discontinuation***	***Post-intervention***
	Timepoint	Day -14	Day -14 to day -7	Week 0	Weeks 1–12	Week 6	Discontinuation prior to week 12	Weeks 13–14
**Assessment/procedure**	Advertising of study	x						
	Pre-screening risk assessment	x						
	Inclusion and exclusion criteria		x					
	Participant information sheet		x					
	Informed consent form		x					
	Adult Pre-Exercise Screening System (APSS) (stages 1 and 2)		x					
	Assessment by medical officer of medical fitness to participate in physical activity		x					
	Baseline interview (demographics; incarceration history; perceived health status; psychiatric history)			x				
	Clinical assessment of cardiometabolic risk (APSS stage 3) • Body mass index (BMI) • Waist and hip circumference • Resting blood pressure • Lipid profile (total cholesterol, HDL, LDL, triglycerides) • Liver function • Blood glucose (HbA1c; fasting glucose)			x			x	x
	Current Community Assessment of Psychic Experiences-Positive Scale (Current CAPE-P15)			x				x
	Depression Anxiety Stress Scale (DASS-21)			x		x	x	x
	Simple Physical Activity Questionnaire (SIMPAQ)			x		x	x	x
	OMNI-Walk/Run Scale of Perceived Exertion*				x			
	YMCA Step Test (VO_2_max testing)			x			x	x
	Dynamic Appraisal of Situational Aggression (DASA)				x			
	Adverse event check				x		x	x
	Compliance and adherence assessments				x			
	Participant acceptability/perceived utility survey*						x	x
	Staff acceptability/feasibility survey*						x	x

* Intervention group only

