#### Secondary outcome measures

##### Potential impact of intervention on mental health

The potential impact of the exergaming intervention will be assessed by measuring baseline to post-intervention changes in mental health outcomes:

**Depression, anxiety and stress:** Symptoms of depression, anxiety and stress will be measured using the Depression Anxiety Stress Scale (DASS-21). The DASS-21 is a 21-item self-report measure of symptoms of depression, anxiety and stress over the previous week [37]. Higher scores on the DASS-21 indicate a greater severity of symptoms. Assessments will be conducted at baseline, intervention mid-point and post-intervention.

**Positive psychiatric symptoms:** Positive psychiatric symptoms will be assessed at baseline and post-intervention using the Current Community Assessment of Psychic Experiences-Positive Scale (CAPE-P15) [38], a 15-item self-report scale that measures the frequency of psychotic-like experiences over the preceding 3 months. The CAPE-P15 comprises three sub-scales (persecutory ideation, bizarre experiences, perceptual abnormalities), with higher scores indicating more frequent symptomatology.

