#### Quantitative data

Quantitative feasibility outcomes will be reported descriptively and narratively. Rates of recruitment, retention, protocol adherence/compliance, intervention fidelity and adverse events will be presented as frequencies and proportions. Participants recruited to the study in the initial wave (January–March 2020), prior to the suspension of recruitment during the COVID-19 outbreak in NSW (March–June 2020), will be replaced by new participants to achieve the target sample size and will have their data excluded from the final analysis.

Primary and secondary outcomes will be analysed descriptively and presented for the overall sample and by group. Means, standard deviations and ranges, or medians and interquartile ranges, as appropriate, will be reported for continuous data, and frequency counts and proportions for categorical data, with associated 95% confidence intervals. Missing data for each of the primary and secondary outcome measures will be described using descriptive statistics. Missing data will not be replaced or imputed.

As this pilot study primarily aims to determine the feasibility of conducting a future definitive intervention trial and is not powered for statistical hypothesis testing, statistical analysis of the potential effectiveness of the intervention will not be performed on the clinical outcome data. Physical activity, cardiorespiratory fitness, and cardiometabolic risk data collected at each timepoint will be summarised descriptively for each group. Whilst between-group statistical comparisons will not be undertaken, post-intervention differences between groups will be reported using estimated mean differences and 95% confidence intervals, where appropriate.

Perceptions of exercise intensity, general health status and the study experience will be reported descriptively and narratively. All analyses will be performed using IBM SPSS software (Version 27) [40].

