### Strengths and limitations

A strength of the FIT HEART study is that it is the first to investigate the feasibility and acceptability of exergaming in a psychiatric inpatient setting and assess the potential impact of such an intervention on risk factors for cardiovascular and metabolic disease. Moreover, to our knowledge, it is the first study to trial an exergaming intervention in a correctional mental health facility.

This is a non-randomised and unblinded study and, as such, is potentially susceptible to bias and confounding, limiting the ability to draw causal inferences about the effectiveness of the intervention and generalisability of the findings to the target patient population. The study will be conducted in an inpatient setting, across two high-secure hospital wards, with patient placement according to level of acuity of psychiatric illness. Individual randomisation of participants to the control and intervention groups is not practical and will increase the risk of treatment contamination, as it will not be possible, within a particular ward, to ensure that participants in the control group avoid exposure to the intervention components. The use of a prospective design and a concurrent control group, however, will help to minimise selection bias associated with non-random allocation. Given the nature of the intervention, it is not feasible to blind participants and unit staff to the study conditions. By utilising objective measures of clinical outcomes (i.e. levels of physical activity, cardiovascular fitness, cardiometabolic risk), the risk of performance bias due to awareness of the intervention allocation will be reduced.

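### Table 1 leaves the CAPE-P15 out of the early-discontinuation visit although the text says early leavers get the post-intervention assessments, so early leavers would have only a baseline score on this secondary outcome

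*Protocol article*

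**What the plan says.** The protocol article gives two accounts of what an early leaver completes.

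- **Text, Participant timeline.** If a participant is discharged from the unit or discontinues before week 12, "post-intervention assessments will be administered, where feasible". No instrument is excepted. The Data collection section adds that the post-intervention interview covers every primary and secondary outcome apart from feasibility and acceptability. Positive psychiatric symptoms are one of the two secondary outcome domains.
- **Table 1, same section.** The row "Current Community Assessment of Psychic Experiences-Positive Scale (Current CAPE-P15" is marked at baseline and post-intervention. Its mid-point and early-discontinuation cells are empty. The row "Depression Anxiety Stress Scale (DASS-21" is marked at baseline, mid-point, early discontinuation and post-intervention.

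The Secondary outcome measures section agrees with the table on timing: "Positive psychiatric symptoms will be assessed at baseline and post-intervention using the Current Community Assessment of Psychic Experiences-Positive Scale (CAPE-P15". It gives the scale a recall period of three months. On missing values, the Quantitative data section says: "Missing data will not be replaced or imputed". The Strengths and limitations section describes the wards as high-secure, "with patient placement according to level of acuity of psychiatric illness".

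**The concern.** Staff at an early-discontinuation visit will work from the schedule. The text itself sends the reader to Table 1 for the detail, and Table 1 is the only place where the early-discontinuation assessments are listed one by one. Someone following it would give the DASS-21, the activity questionnaire, the step test and the cardiometabolic assessment, and would leave out the CAPE-P15.

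The CAPE-P15 is more exposed to this than the other secondary measure. The DASS-21 has both a mid-point and an early-discontinuation assessment. The CAPE-P15 has neither, and nothing is imputed, so its change score would come from completers alone.

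This matters because of how people come to leave. Placement depends on psychiatric acuity, so departure from a ward can be related to psychiatric state, which is close to what the scale measures. The plan intends to report estimated post-intervention differences between groups with confidence intervals and to use the findings to form hypotheses for a randomised trial. Symptom-related missingness in this outcome would carry into both.

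**Working it through.** **1. Table against text.** Eight rows of Table 1 carry a mark in the post-intervention column:

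| Row | Early discontinuation | Post-intervention |
|---|---|---|
| Cardiometabolic assessment (APSS stage 3) | marked | marked |
| CAPE-P15 | **empty** | marked |
| DASS-21 | marked | marked |
| SIMPAQ | marked | marked |
| YMCA step test | marked | marked |
| Adverse event check | marked | marked |
| Participant survey | marked | marked |
| Staff survey | marked | marked |

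Seven of the eight agree with the text rule; the CAPE-P15 is the exception. The cell positions were checked against the column headings by splitting each row at its tab positions, so the empty cell is not an effect of how the table was extracted.

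**2. How many participants are exposed.** Inputs from the Sample size section: 30 per arm; attrition allowance 20%; attrition of 7–19% in the cited outpatient and non-psychiatric samples. The plan's total is 2 × 30 = 60, which reproduces. It is not power-based, so there is no power calculation to check.

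Number exposed = 60 × attrition rate:

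- 20%: 60 × 0.20 = 12, or 30 × 0.20 = 6 per arm, leaving 24 per arm with a change score
- 19%: 60 × 0.19 = 11.4
- 7%: 60 × 0.07 = 4.2

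Under Table 1 none of these would have a follow-up CAPE-P15. Under the text rule up to all of them would, subject to feasibility.

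**3. What an early score would cover.** Assumption: three months is about 13 weeks. The share of the recall window that lies before baseline, for an assessment at week w, is (13 − w)/13:

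- week 3: 10/13 = 77%
- week 6: 7/13 = 54%
- week 9: 4/13 = 31%

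An early CAPE-P15 is therefore diluted, heavily so in the first weeks. The DASS-21 and SIMPAQ, which are marked at that visit, look back one week and do not have this problem.

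**The case against.** The strongest reply is that the table may be deliberate. The general sentence is followed at once by a pointer to Table 1, the Secondary outcome measures section also names only baseline and post-intervention, and the Strengths and limitations section treats the early-discontinuation assessments as a set of their own. A three-month recall is a sensible reason to leave the scale out of a visit at week 3 or 6. This stands as a possible explanation, but the article does not give it, and the text rule makes no exception.

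The consequences are also limited. The feasibility qualifier means that a score was never guaranteed, and an acutely unwell patient may be unable to complete a self-report scale. Outcomes are summarised descriptively, missing data will be described for each outcome, and the CAPE-P15 plays no part in the progression criteria. All of this stands and keeps the point modest.

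Two stronger readings are tempting, and the documents support neither.

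- **That a harm signal is lost.** The CAPE-P15 is a secondary outcome and is not described as a safety measure. Safety monitoring and reporting provides for daily adverse event monitoring by interview and record review, with events recorded whether or not they are thought to be caused by the study. The row "Adverse event check" is marked at early discontinuation, and the Study feasibility section has reasons for withdrawal documented. Deterioration can be seen through these routes; what they do not supply is a scale score.
- **That the direction of bias is known.** Placement by acuity does not say that worsening patients are the ones who leave. The departures named are discharge, release, transfer and discontinuation, and improving patients may move out too. If 20% leave and differ from completers by an assumed 0.5 or 1.0 SD, the completers' mean change is off by 0.20 × 0.5 = 0.10 SD or 0.20 × 1.0 = 0.20 SD. The sign could be either, and the SD values have no source in the article.

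**Conclusion.** The inconsistency is real: Table 1 and the text above it disagree on whether early leavers complete the CAPE-P15, and the disagreement decides what is collected. If the table is followed, up to 12 of 60 participants (6 per arm, assuming equal attrition) would have a baseline score only, or about 4 to 11 at the cited attrition rates. Those rates come from other settings, and the article itself expects release and transfer to make retention difficult.

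The resulting missingness may be related to symptoms, because placement depends on acuity. The documents do not allow its direction or size to be stated, and they do not support a claim that deterioration would go unseen. This is a modest, easily corrected gap in a named secondary outcome, and it does not affect the feasibility conclusions.

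**What to change.** - **Table 1.** Mark the CAPE-P15 in the early-discontinuation column, so that the table agrees with the text rule and with the other seven rows.
- **Data collection.** Record the study week of each early-discontinuation CAPE-P15, so that the overlap of its recall window with the pre-baseline period is known.
- **Reporting.** Present early-discontinuation scores separately from the weeks 13–14 scores, and show the change with and without early leavers. This can go in the statistical analysis plan that the article says will follow; its absence from the article is not a fault.

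The cost is one mark in the table and 15 items at a visit already planned. The drawback is the three-month recall: for someone leaving at week 6 about half the window precedes baseline, which limits what the score shows and is why it should not be pooled silently with the completers' scores. If the omission was intended, a sentence stating and justifying the exception would remove the contradiction, but the early leavers' scores would still be missing.

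The article appeared in June 2022 and expects recruitment to run to December 2022, so the change could still have applied to later participants. For anyone who left earlier without the scale, the report should say so.
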